## Lifestyle Considerations

During this study, participants are not asked to modify lifestyle or diet apart from standard of care peri-procedural measures prior to distal pancreatic resection or open pancreaticoduodenectomy.

## Strategies for Recruitment and Retention

This study will be conducted in the United States. Participants for this study will primarily be recruited from GI and surgical practices within OHSU and its affiliated community partners, but additional collaborative study sites may also be invited to participate in this trial. Participants may be identified and referred to this study by their primary treating physician from within OHSU, collaborating study sites, or from the outside community. Participants may be identified by a member of the participant’s treatment team, the PI, research team, or medical and surgical oncology clinics part of OHSU or collaborating study sites. As a member of the treatment team, the investigator(s) will screen their participant’s medical records for suitable research study participants and discuss the study and their potential for enrolling in the research study. Referral of potential participants to investigator(s) of this study is made as part of standard of care, with the referring physician seeking advice on the diagnosis, evaluation, and/or treatment of the participant’s malignancy.

The investigator(s) may also screen the medical records of potential participants with whom the investigator does not have a treatment relationship. This will be done for the limited purpose of identifying patients who would be eligible to enroll in the study and to record appropriate contact information in order to approach these potential individuals regarding the possibility of participating in the study. Participants may also initiate contact with the investigator through information of this study posted on the clinicaltrials.gov website.

- - 1. Accrual Estimates

Total accrual of all participants is anticipated to take a total of 12 months.

No OHSU Knight Cancer Institute study will focus on any particular gender, racial or ethnic subset. No participant will be excluded from the study on the basis of gender, racial or ethnic origin. Male, female and minority volunteers will be recruited for this study from the general population and approximately 50% men and 50% women will be studied. Gender-nonconforming and gender-fluid individuals as members of the general population will also be recruited. Pregnant persons, decisionally impaired adults and prisoners are excluded from this study.

| **Table 1.** **Population Demographics - Oregon (%)** | | | | | |
| --- | --- | --- | --- | --- | --- |
| **Ethnic Category** | **Sex/Gender** | | | | |
|  | Females | | Males | | Total |
| Hispanic or Latino |  | 6.6 |  | 6.5 | 13.1 |
| Not Hispanic or Latino |  | 43.8 |  | 43.1 | 86.9 |
| **Ethnic Category: Total of all participants*** |  |  |  |  | 100* |
|  | | | | | |
| **Racial Category** |  | | | | |
| American Indian or Alaskan Native |  | 0.9 |  | 0.9 | 1.8 |
| Asian |  | 2.4 |  | 2.3 | 4.7 |
| Black or African American |  | 1.1 |  | 1.1 | 2.2 |
| Native Hawaiian or other Pacific Islander |  | 0.2 |  | 0.2 | 0.4 |
| White |  | 43.9 |  | 43.2 | 87.1 |
| Two or more races |  | 1.9 |  | 1.9 | 3.8 |
|  | | | | | |
| **Racial Category: Total of all participants*** |  | |  | | 100* |
| TOTALS |  | 50.4 |  | 49.6 | 100* |
| **Source:** Adapted from U.S. Census Bureau, 2017.  *Totals may not equal 100 due to rounding. | | | | | |

**Table 2. Projected Accrual for the Present Study**

| **Ethnic Category** | **Sex/Gender** | | | |
| --- | --- | --- | --- | --- |
|  | Females | Males | Other/Unknown | Total |
| Hispanic or Latino | 3 | 3 |  | 6 |
| Not Hispanic or Latino | 22 | 21 |  | 22 |
| Unknown | 0 | 0 |  | 0 |
| **Ethnic Category: Total of all participants*** | 25 | 24 |  | 49* |
| **Racial Category** |  | | | |
| American Indian or Alaskan Native | 0-1 | 0-1 |  | 0-2 |
| Asian | 1 | 1 |  | 2 |
| Black or African American | 1 | 1 |  | 2 |
| Native Hawaiian or other Pacific Islander | 0-1 | 0-1 |  | 0-2 |
| White | 22 | 21 |  | 43 |
| More than one race | 1 | 1 |  | 2 |
| Unknown | 0-1 | 0-1 |  | 0-2 |
| **Racial Category: Total of all participants*** | 28 | 27 |  | 55* |
| **Source:** Adapted from U.S. Census Bureau, 2017.  *Totals may not equal 100 due to rounding. | | | | |

- - 1. Inclusion of Children

This protocol does not include children for the following reason:

1. The number of children with this type of cancer/condition is limited

# PARTICIPANT SCREENING, ENROLLMENT, AND WITHDRAWAL

This is a single-arm phase II clinical trial (without randomization).

Each individual that consents to participate in this study must be entered into OHSU’s electronic clinical research information system, eCRIS, regardless of Screening outcome.

## Consent and Screening

In order to participate in this study, signed informed consent must be obtained from the participant or the participant's legally acceptable representative. The current IRB approved informed consent form must be signed and dated by each participant prior to undergoing any study procedures or before any prohibited medications are withheld from the participant in order to participate in this study. The informed consent discussion must be documented, and a copy of their signed IRB approved informed consent form must be scanned in the participant’s medical record.

Each site will maintain a screening log of all participants who are approached for the study, as well as source documentation related to the consent and screening outcome for each, including an explanation for exclusion due to screen failure where applicable. Each site is required to retain, in a confidential manner, sufficient information on each participant so that the participant may be contacted should the need arise.

For consenting subjects with Limited English Proficiency, a short consent will be provided in the subject’s native language. Consenting for patients with limited English proficiency will only be done by a member of the study team if said member is certified by OHSU’s language services to interact with patients in the corresponding language.

For languages other than English and if the study team member is not certified to interact with patients in that language directly, a short form of consent in the subject’s native language will be used only when an interpreter is present. Short forms must be in the subject’s native language. If no interpreter is available, consent for Limited English Proficiency participants will not happen.

- - 1. Screening Period

The screening period begins once the participant has provided written informed consent to participate in the study and ends once ICG injection is initiated. All screening and baseline evaluations will be performed during the screening period. Day 1 of the clinical trial will be when participants are started on the study intervention.

- - 1. Re-testing During Screening

Re-testing of laboratory parameters and/or other assessments within the Screening or Lead-in period will be permitted (in addition to any parameters that require a confirmatory value).

The most current result prior to Enrollment is the value by which study inclusion will be assessed, as it represents the participant’s most current, clinical state.

Laboratory parameters and/or assessments may be repeated in an effort to find all possible well-qualified participants. Consultation with the Principal Investigator may be needed to identify whether repeat testing of any particular parameter is clinically relevant.

## Enrollment Procedures

This is a Phase II trial, and there is no randomization for treatment.

- - 1. Enrollment Procedures for the OHSU Site

Eligibility must be confirmed and documented by the Principal Investigator prior to enrollment.

Materials required to complete the eligibility review include, at minimum:

• Current IRB-approved consent form and HIPAA Authorization for the study signed & dated by the participant

• Documented (signed and dated) attestation by the PI confirming participant’s eligibility based on available source documentation and authorizing enrollment

• Direct surgical evaluation at the time of planned study intervention to verify anatomic eligibility for ICG injection

Once eligibility is confirmed, the participant is considered ‘enrolled’ once study intervention is performed.

## Measures to Minimize Bias

- - 1. Randomization/Masking Procedures

While no randomization of patients will be performed, surgeons will be blinded to ICG perfusion measurements. To avoid undue revision or operative conduct should the gland demonstrate any characteristics (perceived or real) of hypoperfusion, surgeon blinding is key. The blinding will be performed by capturing and analyzing the perfusion images out of view of all non-study personnel obtaining images. Doppler blinding will be conducted using a tape recorder attached to the Doppler unit which disables the speaker.

- - 1. Evaluation of Success of Blinding

A dedicated staff member will evaluate for adequate blinding of the surgeon(s) during perfusion measurements. Measurement of target perfusion tissue with Spy Elite device will only be done when the operator is certain that the surgeon is not watching the device’s screen. The success or failure of adequate blinding will be recorded for each procedure.

The Spy Elite device has a small articulated monitor that will be set up to be facing away from the surgeon. ICG measurements can only be seen on the device monitor and not on other screens in the OR.

If concerns for blinding are noted by the study personnel, these instances will be noted. If no adequate blinding could be achieved ie. There is suspicion that the surgeon saw any of the measurements, these cases will not be used for analysis.

All the surgeons participating in the study are aware of the importance of blinding and that violation of blinding impairs the analysis.

- - 1. Breaking the Study Blind/Participant Code

Because intervention of ICG does not currently change clinical practice, there is no need to break the blinding protocol to the surgeon performing the procedure. Blinding of patients does not apply.

## Screen Failures

Screen failures are defined as participants who consent to participate in the clinical trial but are not subsequently assigned to the study intervention or entered in the study. A minimal set of screen failure information is required to ensure transparent reporting of screen failure participants, to meet the Consolidated Standards of Reporting Trials (CONSORT) publishing requirements and to respond to queries from regulatory authorities. Minimal information includes demography, screen failure details, eligibility criteria, and any serious adverse event (SAE).

Individuals who do not meet the criteria for participation in this trial (screen failure) because of a failing to meet eligibility criteria may be rescreened. Rescreened participants should be assigned the same participant number as for the initial screening.

Any participant that has signed the consent form (for either screening or study participation) but does not meet all of the study eligibility criteria, or meets study eligibility criteria but terminates their participation prior to receiving study treatment, will be considered a screen failure and not counted towards total number of planned enrollments. The reason for screen failure should be captured in the research record for each participant who fails to meet all of the eligibility criteria.

- - 1. Re-Screening Allowance / Procedures

This study permits the re-screening of a participant that has discontinued the study as a screen failure (i.e., participant has not been treated). If re-screened, the participant must be re-consented.

## Participant Discontinuation or Withdrawal

Participants are free to withdraw consent and discontinue participation in the study at any time and without prejudice to further treatment. If a participant no longer wants to receive investigational product, but is willing to come for follow-up appointments, the participant’s request should be honored, if possible.

If a participant withdraws consent, they should be asked to specify if they are withdrawing consent to all further participation in the study, including any further follow up (e.g., survival contact telephone calls) or if they are choosing to withdraw only from further study intervention, meaning that further follow-up and data collection about their disease and health status is allowable. The participant should also be asked about their consent to the future use of their study-generated data and any biological samples, as applicable.

No further participant contact should be made if the participant withdraws consent for participation in the study. Information about the reason(s) for discontinuation and collection of any new or ongoing AEs should be collected at the time the participant withdraws consent.

A participant may also be withdrawn from the study by the Sponsor/Sponsor-Investigator, Investigator, local IRB, or regulatory authorities.

Reasons for a participant to discontinue the study may include the following:

• Participant dies or is lost to follow-up

• Participant withdraws consent for any further participation

• The end of study is reached

• Pregnancy

• Significant study intervention non-compliance

• If any clinical adverse event (AE), laboratory abnormality, or other medical condition or situation occurs such that continued participation in the study would not be in the best interest of the participant

• Disease progression which requires discontinuation of the study intervention

• If the participant meets an exclusion criterion (either newly developed or not previously recognized) that precludes further study participation

In the event of a pregnancy, the study treatment will not be administered. Refer to Section 10.6.5 regarding reporting of pregnancy. Participants who withdraw or discontinue after receiving study intervention count towards the enrollment total.

- - 1. Handling Participant Discontinuation from Study

When a participant discontinues participation in the study, the reason the participant is no longer participating, the study name, IRB study number, and the date of discontinuation must be documented in the participant’s medical record. The change in study status must be documented in the appropriate clinical trial management system (e.g., eCRIS) per OHSU policy.

For all other reasons for discontinuation from the study treatment phase, the participant should return to the clinic for the end of treatment (EOT) visit according to Section 8, STUDY PROCEDURES/EVALUATIONS AND SCHEDULE

## Lost to Follow-up

A participant will be considered “lost to follow-up” if the participant:

Undergoes ICG injection and planned surgical intervention but does not present for planned post-operative follow-up appointment and is unable to be contacted by study staff for 30 days following postoperative hospital discharge.

The following actions must be taken if a participant fails to return to the clinic for a required study visit:

- The site will attempt to contact the participant and reschedule the missed visit within two weeks, and counsel the participant on the importance of maintaining the assigned visit schedule and ascertain if the participant wishes to and/or should continue in the study.
- Before a participant is deemed lost to follow-up, the investigator or designee will make every effort to regain contact with the participant (where possible, 3 telephone calls and, if necessary, a certified letter to the participant’s last known mailing address or local equivalent methods). These contact attempts should be documented in the participant’s medical record or study file.
- Should the participant continue to be unreachable, he or she will be considered to have withdrawn from the study with a primary reason of lost to follow-up.

# STUDY INTERVENTION

A list of the adverse events and potential risks associated with the study intervention administered in this study can be found in Section 10.4, Adverse Events.

## Name of Study Intervention

- - 1. Study Intervention Description

**Indocyanine green**: ICG is an FDA-approved intravenous drug that binds albumin and when detected using near-infrared imaging performs well as a marker of blood flow and oxygenation.^26^ When applied intravenously, ICG travels to tissues by arteries. ICG has been used for more than 50 years. ^19^ Since then, studies of ICG both in the lab and in clinical trials, have shown promising results of its use in different surgical procedures. ICG has an excellent safety profile and adds little to no risk to patients undergoing surgery.^23, 24^

Study Device information is detailed in section 6.2, but briefly includes use of the Stryker Spy+ Elite platform. The Stryker Spy+ Elite is an FDA approved imaging system for intraoperative acquisition of near-infrared images and measurement of ICG perfusion kinetics and metrics. ICG uptake data will be measured immediately before reconstruction in the case of pancreaticoduodenectomies and for distal pancreatectomies, during visual inspection of right upper quadrant prior to surgical closure.

- - 1. Acquisition

ICG for Injection is on OHSU Pharmacy Formulary and comes as a single-patient vial of 25mg of lyophilized drug, which is then reconstituted with 10mL of sterile injectable saline.

- - 1. Formulation, Appearance, Packaging and Labeling

ICG is an FDA approved drug supplied as a sterile, lyophilized green powder containing 25 mg of indocyanine green with no more than 5 % sodium iodide. It is packaged with an Aqueous Solvent consisting of Sterile Water for Injection used to dissolve the indocyanine green. ICG is to be administered intravenously.

- - 1. Product Storage and Stability

ICG should be stored at 15° to 25° C.

ICG should be used within 6 hours after it is prepared.

- - 1. Compatibility

ICG should only be prepared with the included aqueous solvent.

- - 1. Handling

FDA data states that ICG is unstable in aqueous solution and must be used within 6 hours. However, the dye is stable in plasma and whole blood so that samples obtained in discontinuous sampling techniques may be read hours later. Sterile techniques should be used in handling the dye solution as well as in the performance of the dilution curves.

- - 1. Preparation

Under sterile conditions, reconstitute one (1) 25 mg vial of Indocyanine Green for Injection, USP using one (1) 10 mL Sterile Water for Injection, USP vial located in the ICG for Injection Set. Shake the ICG vial gently to dissolve. After reconstitution, a 25 mg vial of ICG contains 2.5 mg of dye per mL of solution, so a 1.0 mL injection contains a 2.5 mg dose of ICG.

Indocyanine Green for Injection, USP must be used within 6 hours after reconstitution. If a precipitate is present, discard the solution.

- - 1. Administration

ICG is for intravenous use. All administration of ICG as part of this study will be through a peripheral intravenous line or a central line placed at the discretion of the anesthesiologist for the purpose of medication administration as a standard part of the operation. Administration of the dye plus measurement of tissue perfusion is an additional step that is not done in conventional pancreatectomies. Based on studies looking at ICG use in other gastrointestinal surgeries, we can expect an increase of operative time of 10-15 minutes. Data shows that this increase in operative time when using ICG versus not using this technology is not statistically significant. ^26,27^ Study staff in the operating room will measure the time to get information on the impact of normal workflow of these surgeries. Additionally, need of repeat doses of ICG will be recorded and compared to operative time to measure the impact. Upon completion of the study, descriptive statistics will be reported to analyze the impact of ICG use and perfusion measurements on pancreatic surgeries.

- - 1. Special Considerations for Administration

Heparin preparations containing sodium bisulfate reduce the absorption peak of ICG in blood and, therefore, should not be used as an anticoagulant for the collection of samples for analysis. Drug/Laboratory Test Interactions: Radioactive iodine uptake studies should not be performed for at least a week following the use of ICG.

During IV administation of ICG, vital signs will be continously monitored for any change from normal parameters. All subjects will have their heart rate, respiratory rate, oxygen saturations, blood pressure and ventilation will be monitored throughout and after the procedure. If subjects develop hypersensitivity symptoms like rash, wheezing, or pruritus, hypersensitivity medications should be administered.

There are no other special considerations, including hydration, steroids, special IV tubing, filtration, or special equipment required.

Physician administering IV ICG must wear sterile gloves and use sterile technique when using ICG.

- - 1. Accountability

The Investigator, or a responsible party designated by the Investigator, must maintain a careful record of the inventory and disposition of the study agent. (See the [NCI Investigator’s Handbook for Procedures for Drug Accountability and Storage](http://ctep.cancer.gov/investigatorResources/investigators_handbook.htm)).

As this protocol specifies an investigational application of an FDA approved substance which is on-formulary at OHSU, storage, tracking, inventory, and return will be tracked by the OHSU Pharmacy as per current standard operating practices. Utilized drug details including but not limited to dose, expiration date, manufacturing date, and lot number will be recorded for participants.

Responsibility for drug accountability at the study site rests with the Investigator; however, the Investigator may assign some of the drug accountability duties to an appropriate pharmacist or designee. Inventory and accountability records must be maintained and readily available for inspection by the study monitor and are open to inspection at any time by any applicable regulatory authorities or other oversight bodies.

The Investigator or designee will collect and retain all used, unused, and partially used containers of study medication until full accounting has been completed. The Investigator or designee must maintain records that document:

- Investigational product delivery to the study site.
- The inventory at the site.
- Use by each participant including pill/unit counts from each supply dispensed.
- Return of investigational product to the Investigator or designee.
- Destruction or return of investigational product for final disposal.

These records should include dates, quantities, batch/serial numbers (if available), and the unique code numbers (if available) assigned to the investigational product and study participants.

The investigational product must be used only in accordance with the protocol. The Investigator will also maintain records adequately documenting that the participants were provided the correct study medication specified.

Completed accountability records will be archived by the site.

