| **Secondary Objectives** | Evaluate the grade of leak via ISGPS classification and ICG metrics  Determine feasibility of intraoperative measurement of pancreatic perfusion using ICG and the SpyElite platform via a survey to be completed by OR staff.  Evaluate logistics of intraoperative perfusion measurement for staff and operating room using a survey. |
| **Primary Endpoint** | Incidence of biochemical leak or fistula after pancreatectomy defined by definitions of the ISGPS criteria |
|  | |
| **Key Inclusion Criteria** | Patients undergoing open pancreaticoduodenectomy or distal pancreatectomy for any diagnosis will be evaluated for inclusion. |
| **Key Exclusion Criteria** | Development of intra- or post-operative occurrences known to be associated with postoperative pancreatic fistula including hemorrhage, intraoperative blood transfusion, sustained postoperative hypotension requiring vasopressor support, unexpected ICU transfer, initiation of ACLS protocols will be excluded.  Patients with adverse reactions or allergies to indocyanine green will be excluded. History of prior pancreatectomy, prior severe pancreatitis, history of chronic pancreatitits, visceral vascular abnormalities, severe atherosclerosis, planned vascular reconstruction, hepatic insufficiency, liver fibrosis or cirrhosis will be excluded. |
| **Number of Participants** | *n* = 50 patients; anticipate screening *n =* 75 individuals. |
| **Duration of Therapy** | One 5.0 mg IV dose of indocyanine green, intraoperatively, with repeat intraoperative dosing up to maximum 2mg/kg |
| **Duration of Follow Up** | Thirty (30) days. |
|  | |
| **Description of Study Intervention** | Study participants will undergo one intraoperative measurement of pancreatic remnant perfusion. This involves intravenous administration of indocyanine green dye during their operation followed by immediate near-infrared perfusion measurement using the Stryker SpyElite camera, targeted at the organ of interest prior to drug administration. The intervention is expected to take five minutes total. |
|  | |

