# STUDY DESIGN

## Description of the Study Design

*Refer to* Section 11*, Statistical Analysis for additional information regarding statistical methods used in this study.*

This is a Phase II study to assess diagnostic parameters of hypoperfused pancreatic cut edge via ICG and its relation to fistula formation versus conventional measurements. The study design consists of a single arm intervention group (n=50).

The trial will commence with the enrollment of the fifteen patients, after these 15 casesa logistics run-in of the OR ICG technique and timing will be done. During the logistics run-in, the PI will evaluate team satisfaction and measurement outcomes. This will be done through the application of a 3-question paper-based quality survey, attached in the supporting documents for the protocol. If an average score below 50% is given, study will be terminated to avoid negative impact on the logistics of pancreatectomies. Survey scores are calculated depending on the answer given, A= 0% B = 16.5% C = 33%. Minimum score 0 maximum score 100. Progressive study enrollment will continue throughout the adjustments, and enrollment will be halted if any major concerns arise. If the interim analysis does not result in study termination, enrollment of the remaining participants will resume to enroll a total of 50 patients completing study intervention and follow-up.

Aside from interim analysis evaluating logistics. A patient safety analysis will be performed at the same time. Herein, potential factors of the clinical trial that could negatively impact patient outcomes will be addressed. These factors include adverse effects of ICG administration and factors from the clinical trial process that negatively impact the conventional treatment course of patients. If any concerns are identified on interim safety analysis, the study could temporarily pause enrollment until the issues are addressed. This is to supplement study stopping rules delineated in 9.6 and Data and Safety forms.

The study schedule will be divided into 2 periods: (1) the intra-surgical period which starts at the time of ICG injection and ends when the surgical procedure is terminated and (2) the postoperative period which begins at the end of surgery and ends 30 days postoperatively.

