# STUDY POPULATION

## Participant Inclusion Criteria

To be eligible to participate in this study, an individual must meet all of the following criteria:

1. Participant scheduled for open pancreaticoduodenectomy or distal pancreatectomy for any diagnosis
2. Participant ≥ 18 years of age
3. Ability to understand nature and individual consequences of clinical trial
4. Written informed consent from participant or legally authorized representative.
5. For participants of childbearing potential, a negative pregnancy test and adequate contraception until 14 days after trial intervention
6. Participant needs to have an operative drain (any closed suction drain) after the procedure.
7. Participants that do not require arterial reconstruction
8. Participants that require minor portal venous recounstructions including patch venoplasty

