# TREATMENT PLAN

## Dosage and Administration

| **Regimen Description** | | | | | |
| --- | --- | --- | --- | --- | --- |
| *Agent* | *Premedication; Precautions* | *Dose* | *Route** | *Schedule* | *Cycle Length* |
| Indocyanine green | none | 5.0 mg | IV | During surgery | Single injection; may be repeated to maximum dose of 2mg/kg |
| **Specify route of administration (e.g., IVB, IVP, IVCI, PO, intra-arterial, peritoneal, intrathecal, intracavity, etc.) and duration (e.g., IVP over 10 seconds), including any allowable time windows (+/- minutes).* | | | | | |

Repeated doses of ICG could be considered if the initial dose does not create adequate uptake in reference tissue when creating a baseline to then compare with the cut edge of the pancreas. Adequate uptake will be defined as a change of ICG detected by the Spy Elite+ device when compared to tissue before ICG administration. Repeated doses of ICG injections while staying under the maximum dose would not significantly increase risk for adverse reactions. However, requiring additional doses of the dye could increase total operative time. Impact of operative time with use of ICG is further addressed in 6.1.8. “ADMINISTRATION”.

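### Total operative time is too coarse a yardstick for the time cost of repeat ICG dosing; the ICG step itself should be timed

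*Protocol*

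**What the plan says.** Section 5.0.7 (Administration) treats ICG injection and imaging as a step added to the usual operation. Citing other gastrointestinal surgery, it states that "we can expect an increase of operative time of 10-15 minutes". It then gives three commitments in sequence:

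- "Study staff in the operating room will measure the time to get information on the impact of normal workflow of these surgeries".
- "need of repeat doses of ICG will be recorded and compared to operative time to measure the impact".
- At study end, "descriptive statistics will be reported to analyze the impact of ICG use and perfusion measurements on pancreatic surgeries".

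Section 6.0 (Dosage and Administration) allows a repeat dose when uptake in the reference tissue is inadequate. It warns that "requiring additional doses of the dye could increase total operative time" and sends the reader to the Administration section for the effect on operative time. The word total appears there, not in Section 5.0.7.

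The synopsis gives a shorter duration for the procedure: "The intervention is expected to take five minutes total".

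Section 2.0 describes a single arm of 50 patients. Section 3.0 admits two operations: "Participant scheduled for open pancreaticoduodenectomy or distal pancreatectomy for any diagnosis". Section 5.0.0 places imaging before reconstruction in one and before closure in the other. For the repeat-dose comparison, no separation by operation is stated.

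**The concern.** The protocol itself fixes the yardstick here. What it wants to learn is the time added by another injection, which is a matter of minutes. What it sets against the repeat dose is the length of the whole operation, in a group that mixes two different procedures. The variation in that length enters the comparison in full.

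The sentence before the quoted one has staff timing something, but it does not say whether this is the ICG step or the operation, gives no start or stop, and is not linked to the repeat-dose comparison.

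At stake is a reported difference of tens of minutes, in either direction, that says little about re-dosing. It could be read as evidence on workflow when the follow-on trial mentioned in the study rationale is planned. If the clock times of the step are not captured in the operating room, no later analysis plan can recover them.

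**Working it through.** **The plan's own figures.** The protocol states no precision, sample size or power for this comparison, so there is nothing to reproduce. The 10-15 minutes comes from cited studies and cannot be re-derived from the document.

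**Inputs from the protocol.** N = 50, single arm (Section 2.0). Two operations (Section 3.0). Expected time for the whole ICG step: 5 minutes (synopsis) to 10-15 minutes (Section 5.0.7). Time added by a repeat dose: not given.

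**Inputs assumed, because the protocol gives none.** Standard deviation (SD) of operative time 30-120 minutes. Share re-dosed 10-50%. Gap in mean duration between the two operations 60-120 minutes. Difference in operation mix between repeat-dose and single-dose patients 10-30 percentage points. SD of the timed ICG step 2-5 minutes.

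**Step 1: precision on operative time.** For repeat-dose minus single-dose patients,

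SE = SD × √(1/n_repeat + 1/n_single), and 95% half-width = 1.96 × SE.

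Most favourable corner (25 v 25, SD 30): SE = 30 × √(1/25 + 1/25) = 8.5, half-width 16.6 minutes.
Least favourable corner (5 v 45, SD 120): SE = 120 × √(1/5 + 1/45) = 56.6, half-width 110.9 minutes.

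Half-widths in minutes:

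| Repeat v single | SD 30 | SD 60 | SD 90 | SD 120 |
| --- | --- | --- | --- | --- |
| 5 v 45 | 27.7 | 55.4 | 83.2 | 110.9 |
| 10 v 40 | 20.8 | 41.6 | 62.4 | 83.2 |
| 15 v 35 | 18.1 | 36.3 | 54.4 | 72.6 |
| 25 v 25 | 16.6 | 33.3 | 49.9 | 66.5 |

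Every cell exceeds 15 minutes, the top of the range expected for the whole step. Even with a 25 v 25 split, the half-width falls below 15 minutes only if SD < 15 / (1.96 × √(2/25)) = 27 minutes.

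**Step 2: case mix.** If the share of pancreaticoduodenectomies differs between repeat-dose and single-dose patients, the difference in means shifts by gap × difference in share: from 60 × 0.10 = 6 minutes to 120 × 0.30 = 36 minutes. If the shares are equal the shift is zero, and pooling the operations only adds spread.

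**Step 3: precision if the ICG step is timed.** Same formula, step SD 2-5 minutes, 10-30% re-dosed:

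- 15 v 35, SD 2: 1.96 × 2 × √(1/15 + 1/35) = 1.2 minutes.
- 5 v 45, SD 5: 1.96 × 5 × √(1/5 + 1/45) = 4.6 minutes.

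That is the scale on which an extra injection could be seen.

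**The case against.** The strongest reply is that little depends on this comparison. Section 5.0.7 promises descriptive statistics and no test, so power for a test would answer a question that the protocol does not ask. Operative time is not a listed endpoint. A reader might infer that the secondary objective on logistics is undermined. The documents do not support that: the synopsis and Sections 1.1 and 10.3.2 assess logistics by survey, and the run-in termination rule in Section 2.0 uses the survey score. All of this stands, and it sets the priority.

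The 10-15 minutes refers to using ICG versus not using it. It is not the increment from a repeat dose, and it should not be treated as the true difference between the two groups. This also stands. The working uses it only as a scale for the whole step.

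The lack of an ICG-free group is not a fault of the repeat-dose sentence, since single-dose patients are its comparator. It matters only if operative time is used to show the impact of ICG use as such.

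Finally, the staff timing may already be meant as the ICG step, and tabulation by operation can be left to an analysis plan. The first part is possible, but the text does not define the time or connect it to the comparison. The second is right, but it does not cure the choice of yardstick or secure the clock times.

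**Conclusion.** The point holds as a minor one. Against total operative time, the repeat-dose comparison is likely to be dominated by noise: the 95% half-width is about 17-111 minutes for a step expected to take 5 to 15 minutes in all. This rests on assumed standard deviations of 30-120 minutes and 10-50% re-dosed. The conclusion would weaken only if the standard deviation of operative time across both operations were below about 27 minutes with an even split, or lower still with an uneven one.

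A reader might go further and say that the result will necessarily reflect case mix. The documents do not show this. Section 6.0 makes a repeat dose depend on uptake in reference tissue, and nothing links that to the type of operation. Case mix biases the comparison only if re-dosing differs by operation.

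Priority is low, because no endpoint, decision or stopping rule uses the result.

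**What to change.** In Section 5.0.7, replace the repeat-dose sentence with wording to this effect:

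*The time recorded by study staff is the interval from first ICG injection to end of imaging. It will be summarised for all patients and compared descriptively between patients with a single dose and patients with repeat doses. Total operative time will be described separately for pancreaticoduodenectomy and distal pancreatectomy and will not be used to estimate the effect of ICG or of repeat dosing.*

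Injection is a better start point than preparation, because Section 5.0.6 allows up to six hours between reconstitution and use, so an interval starting at preparation could contain idle time.

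The cost is two clock times per case, taken by staff who are already asked to measure time, and a place to record them. One limitation should be stated: where the step overlaps other work in the room, the interval may differ somewhat from the net time added to the operation. No endpoint, sample size or clinical procedure changes.
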